##### Inclusion criteria

(1) Age ≥18 years.(2) ICU admission with AGI grade I (gastrointestinal dysfunction with risk of failure) or grade II (gastrointestinal dysfunction) according to the 2012 European Society of Intensive Care Medicine (ESICM) (6) diagnostic criteria.(3) Able to initiate enteral nutrition within 24–48 h of ICU admission.

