### Randomization and blinding methods

2.4

Because all enrolled patients initially present with AGI grade I–II, a PBF will be administered for the first 3 study days. On day 4 of the study, gastrointestinal function will be reassessed. Patients reassessed as AGI grade 0–I will be eligible for randomization. Eligible patients will be randomized using block randomization, with a 1:1 allocation ratio to either continued a PBF (PBF group) or transition to an SPF (SPF group). The randomization sequence will be generated in R software (version 4.4.2) using permuted blocks of variable size (4 and 6).

Owing to the nature of the intervention, this is an open-label protocol, and the treating clinical team must be aware of group assignment for intervention delivery (participants may or may not be aware depending on clinical status). To minimize detection bias, feeding intolerance and other outcomes will be assessed and recorded by dedicated research staff who are independent from the ICU clinical team and do not participate in treatment decisions or nursing care.

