### Sample size

2.5

The sample size was estimated in PASS v23 (NCSS, Kaysville, UT; https://www.ncss.com/software/pass/) for the primary endpoint of energy intake on day 7 (kcal/kg/day), comparing two independent groups with equal allocation (1:1). Based on retrospective data, the SPF group had a mean ± standard deviation (SD) intake of 22.4 ± 9.825 kcal/kg/day and the PBF group had 24.9 ± 9.1 kcal/kg/day. Using a two-sided *α* = 0.05 and power (1 − *β*) = 0.90, the required sample size is *n* = 225 per group (total *N* = 450). Allowing for a 10% attrition rate, the target sample increases to *N* = 495. To maintain balance between the two treatment groups under block randomization with variable block sizes of 4 and 6, the final planned sample size is *N* = 496.

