#### Data analysis

2.8.2

All statistical analyses will be conducted in accordance with a pre-specified statistical analysis plan. The primary analysis will follow the intention-to-treat (ITT) principle The Full Analysis Set (FAS) will include all participants who were successfully randomized and entered the intervention period, provided that they have a valid assessment of the primary outcome (caloric intake on day 7) or sufficient information to derive this value. The Per Protocol Set (PPS) will be a subset of the FAS, including participants who received the allocated intervention for at least 72 h and had no major protocol deviations. The PPS will be used for sensitivity analyses to assess the robustness of the primary findings. The SS will include all participants who received at least one dose of the study intervention and will be used for safety analyses.

The primary outcome, caloric intake on day 7 (continuous variable), will be analyzed using a linear regression model. The model will include the intervention group and the predefined covariates (APACHE II score, BMI, AGI grade, and primary diagnosis) as fixed effects. As this is a single-center randomized controlled trial, no random effects will be specified. To account for potential model misspecification and heteroscedasticity, heteroskedasticity-robust (sandwich) standard errors will be used for statistical inference. If the model residuals show substantial deviation from normality or are influenced by outliers, data transformation (for example, logarithmic transformation) or a nonparametric bootstrap method will be applied in sensitivity analyses to assess the robustness of the results.

Continuous secondary outcomes (e.g., the number of days without a ventilator in the ICU) will be analyzed analogously using linear regression models; secondary binary outcomes (e.g., FI) will be analyzed using a generalized linear model (GLM) with a logit link function. The model will include the intervention group and the pre-specified covariates as fixed effects. As this is a single-center study without inter-center or clustering structures, no random effects will be specified. In addition, because FI is a composite secondary endpoint, each FI component will be reported and analyzed separately alongside the composite FI outcome.

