Continuous variables will be summarized as mean ± SD if normally distributed, or as median and interquartile range (IQR, P25–P75) if not normally distributed. Between-group differences in continuous variables will be tested using the independent samples t-test for normally distributed data or the Mann–Whitney U test for non-normally distributed data. Categorical variables will be compared using the Chi-square test.

To assess whether between-group differences in caloric adequacy and tolerance reflect intrinsic physiological effects of the enteral formulas or are confounded by differences in feeding tolerance management, we will compare key nutrition-support process indicators (time to EN initiation; FIS-guided feeding-rate adjustments every 4–6 h; use of prokinetic and/or anti-diarrheal agents; post-pyloric feeding) between groups during the intervention period and will add these as covariates for adjusting confounding factors. At the same time, we will conduct sensitivity analyses to test the robustness of the results.

Sensitivity analyses will include: (I) an unadjusted GLM including only the treatment factor; (II) a covariate-augmented GLM including the prespecified covariates APACHE II score, AGI grade, BMI, primary diagnosis as well as baseline mechanical ventilation. (III) Key treatment indicators include time to initiation of enteral nutrition, feeding-rate adjustments at 4–6-h intervals based on the FIS score, use of prokinetics or antidiarrheals, and use of post-pyloric feeding. All covariates are prespecified and will be retained in the models regardless of statistical significance.

Adjusted odds ratios (ORs) with 95% confidence intervals (CIs) will be reported for binary outcomes, with standardized marginal risk differences provided as supplementary estimates. The primary endpoint will be tested at a two-sided *α* = 0.05 level without multiplicity adjustment. For prespecified secondary clinical endpoints, the false discovery rate (FDR) will be controlled at q = 0.05 using the Benjamini–Hochberg procedure based on two-sided *p* values from the specified models.

Process outcomes (such as fidelity, exposure, and contamination) will be treated as exploratory outcomes and summarized descriptively with 95% CIs; no hypothesis testing or multiplicity correction will be applied to these exploratory analyses.

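### The main model for ventilator-free days omits ventilation status at Day-4 randomisation, a likely strong predictor that appears only in a sensitivity model

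*Protocol article*

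**What the plan says.** Section 2.8.2 (Data analysis) sets the primary model for Day-7 energy intake: "The model will include the intervention group and the predefined covariates (APACHE II score, BMI, AGI grade, and primary diagnosis) as fixed effects". It then says that continuous secondary outcomes, with ventilator-free days as its example, are handled in the same way by linear regression with the pre-specified covariates. Mechanical ventilation is not in that list. It appears later in the same section, in sensitivity analysis (II): "a covariate-augmented GLM including the prespecified covariates APACHE II score, AGI grade, BMI, primary diagnosis as well as baseline mechanical ventilation". The p values used for the Benjamini–Hochberg control of the secondary endpoints come from the specified models.

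On timing, section 2.4 (Randomization and blinding methods) places randomisation on Day 4, after a second assessment of gut function: "Patients reassessed as AGI grade 0–I will be eligible for randomization". The inclusion criteria require grade I or II at ICU admission. Section 2.7.2 applies the word baseline to study day 1 when it defines the nutritional biomarkers. Section 2.8.2 dates neither the ventilation covariate nor the AGI grade. Section 2.4 describes permuted blocks of 4 and 6 and mentions no stratification factor.

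**The concern.** In this trial the natural baseline for covariates is the moment of randomisation, Day 4. A patient already off the ventilator then is likely to have many ventilator-free days under either formula, while a patient still ventilated is likely to have fewer. Status at randomisation is therefore probably among the best available predictors of this outcome. The authors judged ventilation worth adjusting for, yet the main model for the outcome it most directly affects leaves it out.

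Two things are at stake. First, variance that this covariate would explain stays in the residual, so the interval is wider than it needs to be. Second, the randomisation as described balances ventilation only by chance, and the four listed covariates can correct an imbalance only as far as they correlate with it. If baseline means study day 1, as in section 2.7.2, even the sensitivity model would use status from three days before randomisation.

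**Working it through.** **Ventilator-free days.** The documents give no share ventilated, no difference between ventilated and non-ventilated patients and no SD for this outcome, so all three are assumptions: share ventilated at randomisation p = 30–70%, gap in mean ventilator-free days 4–12, within-group SD 9.

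For a binary covariate, R² = p(1−p)·gap² / [p(1−p)·gap² + SD²]. The standard error of the treatment contrast is multiplied by √(1−R²).

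| p | gap (days) | p(1−p)·gap² | R² | fall in SE |
|---|---|---|---|---|
| 30% or 70% | 4 | 3.36 | 3.36/84.36 = 0.040 | 2.0% |
| 30% or 70% | 8 | 13.44 | 13.44/94.44 = 0.142 | 7.4% |
| 30% or 70% | 12 | 30.24 | 30.24/111.24 = 0.272 | 14.7% |
| 50% | 4 | 4.00 | 4.00/85.00 = 0.047 | 2.4% |
| 50% | 8 | 16.00 | 16.00/97.00 = 0.165 | 8.6% |
| 50% | 12 | 36.00 | 36.00/117.00 = 0.308 | 16.8% |

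The comparison is with no adjustment at all. The planned model already holds APACHE II and diagnosis, which may carry part of this information, so the gain over the planned model is smaller by an unknown amount.

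**Chance imbalance.** With 496/2 = 248 per arm, the SD of the between-arm difference in ventilated share is √[2p(1−p)/248].

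- At 50%: 0.045, so a 1.96-SD imbalance is 8.8 percentage points.
- At 30% or 70%: 0.041, so 8.1 points.
- At 85%, outside the range above: 0.032, so 6.3 points.

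Multiplied by a gap of 4–12 days, the shift in an unadjusted contrast is 0.35–1.06 days at 50%, 0.32–0.97 at 30% or 70%, and 0.25–0.75 at 85%. These are extreme draws applied to an unadjusted contrast; the planned covariates would absorb part of the shift.

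**Day-7 energy intake.** Section 2.5 gives the inputs: "SPF group had a mean ± standard deviation (SD) intake of 22.4 ± 9.825 kcal/kg/day and the PBF group had 24.9 ± 9.1 kcal/kg/day". It states: "Using a two-sided *α* = 0.05 and power (1 − *β*) = 0.90, the required sample size is *n* = 225 per group". The difference is 2.5 and the SD is √[(9.825² + 9.1²)/2] = 9.469. Then n per group = 2(1.960 + 1.282)² × 9.469²/2.5² = 302, so 225 is not reproduced at 90% power. At 225 per group, 2.5/[9.469·√(2/225)] = 2.80, and 2.80 − 1.96 = 0.84 corresponds to 80.0% power.

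Now assume that ventilation and AGI grade at Day 4 together add R² of 0.02, 0.05 or 0.10 (not in the documents). The residual SD is 9.469·√(1−R²), and power at 225 per group becomes 80.7%, 81.9% or 83.9%. The gain is about 1 to 4 points, and smaller if the AGI term already is the Day-4 grade. It does not close the gap to 90%: covariates in total would need R² of about 0.25.

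**Availability.** Counting ventilator-free days over 28 days requires ventilation to be tracked over time. Section 2.7.2 does not state when the window starts, but whether it starts at ICU admission or at randomisation, it covers Day 4.

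**The case against.** The strongest case for the plan is that its covariate choice is legitimate. Four prognostic covariates are fixed in advance and kept whatever their significance, allocation is randomised, and almost any trial could add one more predictor. This stands: the planned estimate is valid, and the point concerns efficiency and chance imbalance. A reader might infer that the ventilator-free-day result will be biased; the documents do not support that.

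A reader might also infer that the main models ignore Day-4 status altogether. That is not shown. The undated AGI grade may be the Day-4 grade that decides eligibility, and the separate analysis plan, which is not at hand, may date it. The imputation model in section 2.8.3 also admits other variables related to missingness or outcome, so ventilation is not excluded there.

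Nor is it right that nothing ranks the results if the main and ventilation-adjusted analyses disagree. Section 2.8.2 labels the latter a sensitivity analysis and takes the secondary p values from the specified models.

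Finally, the figures rest on assumed inputs, and the lower end (a 2% fall in the standard error) is trivial. This also stands. It limits how strongly the point can be pressed, but not its direction, and the change costs almost nothing. An unseen analysis plan does not remove the core of the point, because the article itself states both the covariate list and the placing of ventilation in a sensitivity model.

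**Conclusion.** The point holds as a low-cost improvement to a stated method. The main model for ventilator-free days leaves out a covariate that is likely to be strongly prognostic, is known before allocation, and is already used in a sensitivity analysis with no date attached.

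The size of the gain cannot be taken from the documents. The assumed range runs from negligible to material and is an upper bound on the gain over the planned four-covariate model to the extent that APACHE II and diagnosis overlap with ventilation. It also shrinks if nearly all or nearly none of the patients are ventilated at randomisation. Converting these R² values into a number of patients saved would overstate the case, because the comparison would again be with no adjustment.

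For the primary outcome the benefit is small and is no answer to the power shortfall in section 2.5, which is a separate matter. The undated AGI grade is a clarification to make alongside, not an error.

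**What to change.** In section 2.8.2 and the analysis plan:

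1. Define the ventilation covariate as status at Day-4 randomisation, taken from the last record before allocation.
2. Include it in the main model for ventilator-free days. Optionally, add it to the primary model as well, so that one list serves all outcomes; in that case name it in the imputation model of section 2.8.3.
3. State that AGI grade means the Day-4 grade before randomisation, with the ICU-entry grade as an optional second term.
4. Keep the present four-covariate model as the sensitivity analysis for ventilator-free days, so that the effect of the change is visible.

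The cost is a change of wording and one or two degrees of freedom in a trial of 496 patients. No new measurement should be needed, since AGI is graded on both occasions and ventilation must be tracked to derive the outcome. The change should be dated and made before anyone looks at outcomes by arm.

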#### Missing data and interpolation strategies

2.8.3

The proportion of missing data for the primary outcome (caloric intake on day 7) is expected to be approximately 15%, mainly due to discharge, transfer, or incomplete records. The primary analysis will be conducted in the FAS using multiple imputation (MI) under the missing-at-random (MAR) assumption. The imputation model will include treatment group, APACHE II score, BMI, AGI grade, primary diagnosis, and other variables related to missingness or the outcome.

As sensitivity analyses, a complete-case analysis (including only participants with observed day-7 outcomes) will be performed. In addition, PPS analysis and delta-adjusted MI analyses will be conducted to assess the robustness of the results under alternative missing data assumptions.

If the results are consistent across analyses, the study findings will be considered robust.

#### Confidentiality and data security

2.8.4

All collected data will be stored in secure electronic spreadsheets. No individual other than the data administrator will have the authority to modify or export patient data or information. Strict measures will be taken to ensure the confidentiality and security of all patient information. The final trial dataset will be accessible only to the principal investigator, the study statisticians, and authorised members of the trial management committee at the First Hospital of Jilin University. No contractual agreements with sponsors or third parties limit the access of the investigators to the final dataset or their ability to analyse and publish the results.

### Adverse events

2.9

Adverse events are defined according to the CTCAE by the U. S. National Cancer Institute as any unfavorable medical occurrence in a patient receiving the study intervention, which does not necessarily have a causal relationship with the treatment.

Adverse events that may occur during the use of EN in this study include nausea, vomiting, reflux, and gastrointestinal bleeding. Patients will be closely monitored, and appropriate treatment will be provided if symptoms occur. Measures such as elevating the head of the bed will be taken to reduce the risk of aspiration.

## Discussion

3

In patients with impaired intestinal function, the choice of enteral formula is a key determinant of successful EN delivery and of realizing its therapeutic advantages. Multiple guidelines recommend (3, 4, 12, 15) that an SPF should be used as first-line for most critically ill adults, while a PBF may be considered in patients with persistent diarrhea, suspected malabsorption, ischemia, or inadequate response to fiber. However, for patients with intestinal dysfunction after partial recovery of gut function, it remains unclear whether and when to transition from a PBF to an SPF; current guidelines provide no specific recommendations on timing or criteria for such switching. This study protocol is designed to address this evidence gap.

Experimental studies in rats (19–21) indicate that exposure of the colon to N-formyl-methionyl-leucyl-phenylalanine (fMLP) increases the expression of oligopeptide transporters, e.g., Peptide Transporter (PEPT) family, which may aggravate colonic mucosal injury. PBFs could confer a gastrointestinal protective effect by competitively inhibiting fMLP transport and/or leveraging higher transport efficiency through the same carriers, thereby reducing epithelial damage. Additional evidence suggests that (10), compared with SPFs, PBFs accelerate intestinal digestion and absorption of protein, enhance postprandial amino-acid availability, and may increase the rate of skeletal-muscle protein synthesis. Our prior work further showed that (8, 22), versus SPFs, PBFs enabled faster achievement of nutritional targets via EN and were associated with a lower incidence of feeding intolerance. Recent evidence from our team (13) in patients with AGI grade I–II who initiated EN within 48 h, PBFs were associated with greater caloric adequacy and lower incidences of gastric residuals and diarrhea; conversely, among those who initiated EN between days 3–7, SPFs achieved higher caloric adequacy, with no significant differences in gastric residuals or diarrhea between group. These data imply a time-dependent formula preference—PBFs may be more appropriate early, whereas SPFs may be preferable on days 3–7. However, because the study was retrospective, selection bias related to baseline gastrointestinal function cannot be excluded. Accordingly, we designed a prospective, randomized, controlled study to further evaluate, among AGI grade I–II patients who receive PBFs feeding for the first 3 days and whose intestinal function recovers to or remains at AGI 0–I, whether continuing PBFs versus switching to SPFs from day 4 differs in caloric and protein intake, nutritional biomarkers, and intestinal injury markers. We also planned to assess trajectories of muscle mass to clarify whether peptide formulas better support muscle protein synthesis and mitigate muscle loss in critical illness. Key clinical outcomes include mortality, ICU length of stay, ventilator-free time, and the incidence of ICU-acquired infections. Overall, this study will compare the two formulas across nutritional adequacy, feeding tolerance, intestinal protection, muscle preservation, and clinical outcomes, providing clinically meaningful evidence.

This study will exclude patients with chronic liver diseases and severe liver and kidney dysfunction, as these conditions significantly alter energy/protein metabolism, fluid-electrolyte management, and gastrointestinal function. This exclusion is intended to enhance patient safety and reduce metabolic and clinical heterogeneity that could interfere with nutritional delivery and feeding tolerance outcomes. Therefore, our findings are most applicable to ICU patients without chronic liver diseases or severe liver and kidney dysfunction. To improve transparency regarding generalizability, we will report the number of patients excluded due to chronic liver disease or severe renal/hepatic dysfunction in the final report.

This study will use a 3-day run-in with a peptide-based formula and will be randomized only patients who AGI grade 0–I by day 4. This approach standardizes early enteral nutrition and avoids exposing patients with compromised GI function to potentially unsuitable intact-protein formula; however, it may introduce selection bias and reduce external validity. Therefore, our results primarily apply to AGI I–II patients who can tolerate peptide-based enteral nutrition during the early phase and show rapid improvement of GI function, and may not be generalizable to patients with persistent or worsening AGI II.

This study has several notable strengths. 1. To our knowledge, this is the first large randomized controlled trial to address whether, in critically ill patients with AGI whose intestinal function has recovered or at least not worsened, a transition from a PBF to an SPF is necessary. 2. We selected actual caloric intake as the primary endpoint to directly capture the impact of formula type on achieved nutrition, and we complemented this with a broad set of secondary outcomes—including actual protein intake, feeding tolerance, nutritional serum biomarkers, intestinal injury markers, trajectories of muscle mass, and key clinical endpoints—to provide a comprehensive and systematic evaluation. 3. Conducting the trial at a single center is expected to enhance consistency in the feeding protocol and ultrasound measurements. 4. To reduce heterogeneity and confounding, we excluded patients with hepatic or renal disease and those receiving extracorporeal therapies, conditions known to influence metabolism and nutritional requirements (23). 5. Moreover, clinical data are collected by an independent research team that is not involved in patient care, randomization, or data analysis, thereby minimizing subjective bias.

This study also has important limitations. 1. The single-center design may limit external validity and generalizability. 2. Our primary endpoint—caloric intake on ICU Day 7—introduces a risk of missing data among patients who are discharged or die before Day 7; these cases require imputation, which may deviate from true values. 3. Despite standardized training based on the guideline, some team-level subjectivity in implementation is unavoidable and could affect delivered feeding volumes or tolerance management. Although we will adjust for prespecified covariates, co-interventions and variability in feeding strategies may still influence the results, and residual confounding cannot be excluded. Our findings will be interpreted cautiously. 4. Finally, due to resource constraints, indirect calorimetry was not used to set energy targets, which may reduce the precision of prescribed goals.

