#### Primary outcome definition and measures

2.7.1

Energy intake on Day 7, defined as the actual caloric intake on study Day 7 (kcal/kg/day). For patients with BMI > 30 kg/m^2^, an adjusted body weight will be used.

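### Deaths before Day 7 are to be imputed as if a Day-7 intake existed, and the sections on the analysis set, missing data and limitations disagree on whether these patients are imputed or dropped

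*Protocol article*

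**What the plan says.** Section 2.7.1 of the protocol article gives the primary outcome as energy intake on Day 7, "defined as the actual caloric intake on study Day 7 (kcal/kg/day"), with no rule for a patient who has died by then.

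Section 2.8.3 expects the share of missing Day-7 values to be "expected to be approximately 15%, mainly due to discharge, transfer, or incomplete records". Death is not named. On method it says: "The primary analysis will be conducted in the FAS using multiple imputation (MI) under the missing-at-random (MAR) assumption". On the imputation model it says: "The imputation model will include treatment group, APACHE II score, BMI, AGI grade, primary diagnosis, and other variables related to missingness or the outcome".

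The limitations paragraph of the Discussion adds death. It speaks of missing data among "patients who are discharged or die before Day 7; these cases require imputation", and concedes that the imputed values may differ from the true ones.

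Section 2.8.2 limits the Full Analysis Set (FAS) to randomised patients who entered the intervention period and have a usable Day-7 value or enough information to derive one. The Per Protocol Set (PPS) additionally needs at least 72 hours of the allocated formula. The checks listed in 2.8.3 are complete-case, PPS and delta-adjusted imputation analyses. Mortality at 28 and at 90 days is a secondary outcome (2.7.2).

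**The concern.** A patient discharged or transferred alive before Day 7 did take in some amount of energy on Day 7; it was simply not recorded. Imputation is a reasonable tool for that. A patient who died on Day 5 has no Day-7 intake. The limitation's remark that imputed values may differ from true ones presumes a true value that does not exist for this patient.

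What is at stake is the meaning of the primary estimate. If deaths are imputed, it describes intake as though nobody had died. If they are dropped, it describes intake among those still alive. The article does not say which is meant, and its sections point in different directions. In both cases the headline comparison is insensitive to early deaths, although death ends feeding.

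**Working it through.** **Step 1: the sections side by side.**
- Discussion, limitations: death before Day 7 is a reason to impute.
- 2.8.3: the primary method is imputation under missing at random, run in the FAS. Death is not listed as a cause, though the word mainly leaves room for it.
- 2.8.2: the FAS needs a Day-7 value or the means to derive one. Read strictly, a patient who died is outside the FAS, so an imputation run in the FAS never reaches that patient. Read loosely, imputation counts as deriving the value and the patient stays in.
- 2.7.5.1: death closes the exposure window, so for the adherence measures the article already treats death as the end of feeding.

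The article therefore supports two treatments of the same patient and settles on neither.

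**Step 2: do the planned checks separate death from live discharge?**
- Complete-case: drops both alike.
- PPS: randomisation is on Day 4, and from the start of Day 4 to the start of Day 7 is 3 × 24 = 72 hours at most. A patient who dies before Day 7 will in practice not reach 72 hours, so is dropped.
- Delta-adjusted imputation: no separate rule for death is described.

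**Step 3: how far the handling of death could matter.** The article gives no death rate before Day 7, so there is no figure of its own to reproduce on this point. The inputs are the planning means in 2.5 (PBF 24.9, SPF 22.4 kcal/kg/day; difference 24.9 − 22.4 = 2.50) and assumed death shares q_PBF and q_SPF.

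Imputation under missing at random: treatment group is in the imputation model. Leaving other covariates aside, the dead receive their own arm's mean in expectation:

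difference = 24.9 − 22.4 = 2.50 for any q_PBF and q_SPF.

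Dropping the dead gives the same 2.50, the difference among survivors.

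Death scored as 0:

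difference = (1 − q_PBF) × 24.9 − (1 − q_SPF) × 22.4

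| Assumed deaths PBF / SPF | Calculation | Difference |
|---|---|---|
| 3% / 3% | 0.97 × 24.9 − 0.97 × 22.4 | 2.43 |
| 5% / 5% | 0.95 × 24.9 − 0.95 × 22.4 | 2.38 |
| 8% / 5% | 22.908 − 21.280 | 1.63 |
| 5% / 8% | 23.655 − 20.608 | 3.05 |

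With equal shares, the choice hardly moves the mean difference. With a 3-point gap it moves by −0.87 (1.63 − 2.50) or by +0.55 (3.05 − 2.50), depending on which arm has more deaths. At the planned 496 / 2 = 248 per arm, 3 points is about 0.03 × 248 = 7 deaths.

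**Step 4: the price of scoring death as 0.** The variance in an arm becomes (1 − q)(SD² + mean²) − [(1 − q) × mean]². With the planning SDs (9.1 PBF, 9.825 SPF) and 5% deaths in each arm, this is 108.1 for PBF and 115.5 for SPF, a common SD of about 10.57 against 9.47 without deaths. At 248 per arm, power for the expected difference is 0.71, against 0.84 with no deaths. This is a reason to keep that analysis supportive.

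**The case against.** The other side has several sound points.

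A reader might infer that the plan hides any early difference in mortality. It does not. Deaths are compared at 28 and 90 days, all randomised patients are followed to Day 90 (2.7.3), and the exposure window, which closes at death, has its duration reported (2.7.5.4). The insensitivity is confined to the primary outcome.

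A reader might also infer that imputation under missing at random pulls the arms together. With treatment group in the imputation model, that does not follow in general. The expected difference stays at the survivors' difference. It is smaller than the death-as-0 result when deaths are more frequent in the lower-intake arm (2.50 against 3.05) and can be larger in the opposite case (2.50 against 1.63).

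It is tempting to quote one figure per percentage point of excess deaths, using the average of the two means. The arm means differ and the death shares are assumptions, so the documents support no single figure.

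Delta-adjusted imputation cannot be dismissed outright. The article fixes no delta, and a large enough negative shift applied to deaths would come close to scoring them as 0. Such values may properly sit in the analysis plan. What can be said is that the article describes no shift specific to death.

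Finally, several estimands are defensible. An analysis restricted to Day-7 survivors conditions on an event after randomisation, and a zero score mixes mortality with feeding. The documents do not make either the only correct choice.

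What survives all this is that the Discussion names deaths as cases for imputation, no section defines the outcome after death, and the FAS rule points the other way.

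**Conclusion.** The point holds in limited form. As written, the article would assign a Day-7 intake to patients who have died, or exclude them, depending on which section is followed. The primary estimate does not respond to deaths between randomisation and Day 7, and none of the listed checks, as described, treats death separately from live discharge.

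The size is unknown. Only patients with AGI grade 0–I on Day 4 are randomised, so early deaths may be few. The illustrative results (1.63 or 3.05 instead of 2.50) rest on assumed death shares of 5% and 8%, on the planning means, and on the dead being imputed at their own arm's mean. They show that the direction depends on which arm has more deaths; they do not forecast a bias. This should be corrected before analysis, but it does not call the design into question.

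**What to change.** 1. In 2.8.3, separate death from live discharge, transfer and gaps in records, and limit multiple imputation to patients alive on Day 7 whose intake was not recorded.
2. State how death before Day 7 enters the primary estimand, and bring the FAS definition in 2.8.2, the missing-data text in 2.8.3 and the limitations paragraph into line with it.
3. Report the number of deaths before Day 7 by arm beside the primary result.
4. Prespecify one supportive analysis of all randomised patients with death scored as 0 kcal/kg/day.

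The cost is wording and one extra analysis, with no change to design or data collection. There are two drawbacks. If the survivor estimand is chosen, the main model compares groups selected after randomisation. The death-as-0 analysis mixes mortality with feeding and has less power, which is why it stands beside the main model and does not replace it.
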